## Discussion

The purpose of our trial is to assess the efficacy and safety of electroacupuncture compared with sham electroacupuncture treatment in acute decompensated HF patients. Several implications for future acupuncture clinical trials suggested by a previous systematic review were considered for our protocol [24]. The primary outcome of our trial is the total dose of diuretic administered during hospitalization. As excessive diuretics cause electrolyte disorder, which is a risk factor of cardiovascular events [61], decreased diuretic use induced due to acupuncture treatment will prove therapeutic value of acupuncture in HF treatment. Subjective secondary outcomes of our trial include NYHA Functional Classification, the TEAM pattern identification questionnaire [39–43], and QOL questionnaires such as EQ-5D and MLHFQ. Objective secondary outcomes include routine blood tests, cardiac biomarkers, NT-pro BNP, hs-CRP, cardiac function, HRV, and MACE. As we will investigate TEAM pattern identification, we can report distribution of TEAM syndrome in acute HF patients. This study will provide fundamental data for future acupuncture and herbal medicine clinical trials of HF. If possible, subgroup analysis that identifies a response to acupuncture treatment classified by TEAM syndrome differentiation will be conducted. We will also investigate the expectations and credibility of acupuncture, as they are known to affect the therapeutic effect of acupuncture [62, 63]. The efficacy paradox is a well-known phenomenon in the acupuncture clinical trial using a placebo or sham acupuncture. As the effect size of the sham acupuncture treatment is higher than that of placebo medicine, many acupuncture trials have failed to prove the effects of acupuncture compared to placebo acupuncture [64]. Therefore, we tried to decrease the anticipated effect size of the control group. To decrease the effect size of the control group, we adopted PSD in the control group that cannot penetrate skin, selected different acupuncture points for the treatment group, and will use an electric stimulator that does not deliver electricity during control group treatments.

To summarize, our clinical trial protocol adopted several implications for future study from previous reviews that can offer new and sound evidence of electroacupuncture treatment in acute decompensated HF patients.

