### Intervention

#### Study flow

If the participants voluntarily sign informed consent during admission to the cardiology ward, participants will be screened according to inclusion and exclusion criteria on the screening day. After the subject fulfills the criteria, the basic characteristics and prognostic factors of each participant will be evaluated. The subjects will be randomized into an intervention and a control group with a 1:1 allocation ratio on the same day; the screening day and Day 1 will usually be the same day. From Day 1 to Day 5, the participants will receive electroacupuncture treatment or sham electroacupuncture treatment once a day for consecutive 5 days according to their allocated group. After discharge, participants will visit KHMC three times. Visit (V1) will be 7 days after discharge. Visit 2 (V2) will be 28 days after discharge. Visit 3 (V3) will be 180 days after discharge. On the day discharge (Day 5) and V2, blood tests, quality of life (QOL), and a pattern identification questionnaire according to traditional East Asian medicine (TEAM) theory will be evaluated. On V3, cardiac function and MACE will be evaluated by echocardiography (Table 1). Participants will be withdrawn from the study if they 1) re-admit to hospital related to cardiac or kidney dysfunction 2) withdraw of consent by participants 3) worsening cardiac function 4) the principle investigator judged that participants can not continue the research.

**Table 1 Tab1:** Study schedule

Study period	Screening visit	Acupuncture treatment period					Follow-up period		
Visit	Screening	D1	D2	D3	D4	D5	V1	V2	V3
Informed consent	X								
Demographics and history collection	X								
Inclusion and exclusion criteria	X								
Randomization		X							
Physical examination and vital signs check	X	X	X	X	X	X	X	X	X
Body weight	X	X	X	X	X	X	X	X	X
Symptoms check (NYHA Functional Class)	X	X	X	X	X	X	X	X	X
Adverse events	X	X	X	X	X	X	X	X	X
Concomitant medication check	X	X	X	X	X	X	X	X	X
Routine blood test^a^	X		X			X		X	X
NT-pro BNP, hs-CRP	X					X		X	
Cardiac biomarkers^b^		X				X			
Cardiac function (echocardiography)	X								X
Electrocardiogram and HRV		X				X			
QOL and symptom questionnaire^c^		X						X	
Credibility and AES		X				X			
Blinding test		X				X			
Acupuncture treatment		X	X	X	X	X			

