### Outcome measurements: primary endpoint

A detailed outcome measurement schedule is presented in Table 1. The primary outcome of this trial is the cumulative diuretic dose administered from the date of admission to the date of discharge. The total doses of the treatment and control groups will be compared.

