### Outcome measurements: secondary endpoints

Secondary outcomes include both subjective and objective outcomes. Subjective outcomes include symptom improvements measured by the NYHA Functional Classification [38], symptom improvements evaluated by the TEAM pattern identification questionnaire [39–43] and quality of life measured by the EuroQol Five Dimensions Questionnaire (EQ-5D) [44] and the Minnesota Living with Heart Failure Questionnaire (MLHFQ) [45]. Objective outcomes include routine blood tests (renal function and electrolyte imbalance), cardiac biomarkers, NT-pro BNP, hs-CRP, cardiac function measured by echocardiography, HRV, and MACE.

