#### MACE

Mortality due to heart and kidney problems and the readmission rate between the two groups will be compared until 180 days after discharge.

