### Statistical analysis

The primary outcome of our study is the cumulative amount of diuretic administered to each group. After a normality test, the total amount will be compared by an independent *t*-test (parametric) or a Mann-Whitney U test (non-parametric) according to the normality of the data. If the baseline characteristic is significantly different between the two groups, an analysis of covariance (ANCOVA) will be used to adjust the baseline difference. In baseline characteristics and secondary outcome analysis, binary outcomes will be compared by a chi-square test or Fisher’s exact test. Continuous outcomes will be compared by an independent *t*-test (parametric) or Mann-Whitney U test (non-parametric). MACE will be also be analyzed using the survival analysis method. Statistical analysis will be performed using the R package by a blinded statistician. A 5% significance level will be used. Missing values will be replaced by the last observation carried forward method. If there are more than 20% of drop out participants, sensitivity analysis will be conducted including the data.

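### The Discussion takes a lower cumulative diuretic dose as proof of benefit, without tying that conclusion to decongestion or to in-hospital courses cut short

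*Protocol article*

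**What the plan says.** The primary endpoint section defines the outcome: "The primary outcome of this trial is the cumulative diuretic dose administered from the date of admission to the date of discharge". It adds only that "The total doses of the treatment and control groups will be compared". The Discussion then says how a favourable result will be read: "decreased diuretic use induced due to acupuncture treatment will prove therapeutic value of acupuncture in HF treatment". The reason it gives is that too much diuretic disturbs electrolytes and so raises cardiovascular risk.

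Three other places bear on this:

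- **Withdrawal (Study flow).** The criteria for leaving the study include "3) worsening cardiac function 4) the principle investigator judged that participants can not continue the research".
- **Missing data (Statistical analysis).** "Missing values will be replaced by the last observation carried forward method".
- **Death (MACE).** Death appears only within this secondary outcome: "Mortality due to heart and kidney problems and the readmission rate between the two groups will be compared until 180 days after discharge".

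The secondary endpoints section begins its subjective list with NYHA class ("Subjective outcomes include symptom improvements measured by the NYHA Functional Classification") and gives the objective list as follows: "Objective outcomes include routine blood tests (renal function and electrolyte imbalance), cardiac biomarkers, NT-pro BNP, hs-CRP, cardiac function measured by echocardiography, HRV, and MACE". Table 1 has body weight recorded at screening, on each of D1 to D5 and at V1 to V3. Weight is not named in the Objectives, in the secondary endpoints or in the Discussion's list of outcomes.

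**The concern.** The Discussion argues from harm caused by excess diuretic, and a dose is excessive only relative to what the patient needed. The inclusion criteria admit patients with pulmonary edema who need diuretics. In them a lower total may mean that less drug was needed, or that less was given and more congestion remained. These two readings have opposite clinical meaning, and the cumulative dose cannot separate them.

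A shortened course also lowers the total. A patient who dies in hospital, or whose dose record ends at withdrawal for worsening, has fewer days over which to accumulate dose. If the last value of a running total is carried forward, that low figure enters the comparison as a good result.

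At stake is the trial's headline claim. As worded, it could rest on less treatment or a truncated record, even if the other outcomes pointed the other way.

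**Working it through.** **The plan's own figure first.** Inputs from the Sample size calculation section: 223 ± 26 mg and 256 ± 39 mg, two-sided t-test, α = 0.05, power 80%.

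- Design difference: 256 − 223 = 33 mg.
- SD: √((26² + 39²)/2) = 33.14 mg; standardised difference 33/33.14 = 0.996.
- Noncentral t solution: 16.85, so 17 per group (power 0.804).
- With 20% dropout: 17/0.8 = 21.25, so 22 per group.

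Both stated sizes reproduce and are not in dispute.

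**Effect of a truncated record.** The article gives no daily doses and no rate of in-hospital death or withdrawal, so what follows is an illustration. Assumptions: a mean of (223 + 256)/2 = 239.5 mg in both arms; dose spread evenly over 5 days (Study flow and the Table 1 footnote equate D5 with discharge); the running total kept for patients who stop early; all 22 patients per arm analysed; truncation in one arm only.

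- Dose lost by a patient who stops after day 2: 239.5 × 3/5 = 143.7 mg.
- Shift in the arm mean per patient: 143.7/22 = 6.5 mg.
- Four such patients: 4 × 143.7/22 = 26.1 mg, and 26.1/33 = 79% of the design difference.
- Patients needed to reach 33 mg: 33/6.53 = 5.05, so about five.

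Range for four patients, by last day of dosing:

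| Stop after | Shift in arm mean | Share of 33 mg |
|---|---|---|
| day 1 | 239.5 × 4/5 × 4/22 = 34.8 mg | 106% |
| day 2 | 26.1 mg | 79% |
| day 3 | 239.5 × 2/5 × 4/22 = 17.4 mg | 53% |

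Equal truncation in both arms lowers both means alike, so the expected difference moves by about zero.

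**Chance of a false claim.** A simulation took no true effect, mean 256 mg, SD 33.1 mg, normal data, 22 per arm, and stopping after day 2 in the electroacupuncture arm only. The table gives the chance of a significantly lower dose in that arm.

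| Truncated patients | t-test | Mann-Whitney |
|---|---|---|
| 0 | 2.7% | 2.5% |
| 2 | 9.5% | 6% |
| 4 | 33% | 15% |

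These are one-sided worst cases. Four of 22 is 18%, close to the 20% dropout allowance, but the article does not present that allowance as an in-hospital rate.

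**The case against.** The strongest reply is that the sentence is Discussion rationale and not an analysis rule. The endpoint and the test are fixed elsewhere, and rewording the sentence alters neither. That is correct, and the point is about the stated conclusion. But an article that says in advance what its primary result will show has fixed that reading, and an analysis plan not shown does not make the inference follow.

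A reader might infer that the primary result cannot be interpreted at all. The documents do not support this. NT-pro BNP is measured at screening, D5 and V2, and its change is a planned comparison. NYHA class is recorded at every visit. Renal function, electrolytes and MACE are outcomes. The coordinator, assessor, attending physician and participants are blinded, and both arms are managed under the same guidelines, which limits dosing that differs by arm.

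A reader might also infer that four truncated patients would create the whole planned effect. That comes from dividing by 17 (4 × 143.7/17 = 33.8 mg). But 17 is the number before the dropout allowance; if truncated patients stay in the analysis, the divisor is 22.

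Finally, no section says that dose counting stops at withdrawal. The endpoint runs to discharge, and the first withdrawal criterion, re-admission, can only arise after that. So truncation through withdrawal is conditional on how the dose is recorded and how carrying forward is applied. The article does not say how death before discharge enters the dose comparison.

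**Conclusion.** The concern holds in a limited form. The Discussion draws an unconditional conclusion from a dose that can also fall through less decongestion or a shortened in-hospital course. That conclusion is not linked to the decongestion-related outcomes the trial already has, and daily body weight is collected without being an outcome.

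The size depends on imbalance. Under the assumptions shown, each patient stopping after day 2 in one arm shifts its mean by about 6.5 mg, and four by about 26 mg (79% of 33 mg); balanced truncation has about no effect. These figures show sensitivity and do not predict bias. No sample-size figure changes. The fix is worth making because the claim is stated in advance and the data to qualify it are already scheduled.

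**What to change.** 1. In the Discussion, replace the claim of proof with a statement that a lower dose will be read as supporting benefit only alongside the between-group estimates, with 95% confidence intervals, for D1-D5 weight change, NT-pro BNP change at D5 and NYHA class.
2. Name D1-D5 weight change as a secondary outcome.
3. Add a sensitivity analysis of the primary outcome that ranks in-hospital death or withdrawal for worsening as the worst outcome, compared by a rank test, instead of carrying a truncated dose forward.

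Cost: one changed sentence, one added outcome and one added analysis, with no new measurement and no change in sample size. The decongestion estimates will be imprecise with 22 per arm, so they should be reported as estimates and not used as a pass-or-fail gate. Benefit could no longer be claimed from dose alone.

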### Trial status

This trial is currently recruiting participants. Recruitment began on March 26, 2016. We expect recruitment to be complete by the end of 2019.

## Abbreviations

ANS: Autonomic nervous system
BI: Blinding index
BNP: B-type natriuretic peptide
EQ-5D: EuroQol five dimensions questionnaire
HF: Heart failure
HRV: Heart rate variability
hs-CRP: High-sensitivity C-reactive protein
IRB: Institutional review board
KHMC: Kyung hee medical center
KMD: Korean medicine doctor
MACE: Major adverse cardiac event
MLHFQ: Minnesota living with heart failure questionnaire
NT-pro BNP: N-terminal pro b-type natriuretic peptide
NYHA: New York heart association
PSD: Park sham device
QOL: Quality of life
SOP: Standard operating procedure
STRICTA: STandards for reporting interventions in clinical trials of acupuncture
TEAM: Traditional east asian medicine
V1: Visit 1
V2: Visit 2
V3: Visit 3
